## Background

In Burkina Faso, although the national caesarean rate increased from 0.7 % in 2003 [1] to 2 % in 2010 [2], it remains well below the minimum rate of 3 % required to meet the needs [3]. The institutional caesarean rate has risen steadily since the introduction of a policy to subsidize emergency obstetric care in 2006, which significantly increased access to caesareans [4]. Under this policy, caesarean costs are subsidized up to 80 % (100 % in some districts) and transportation is fully funded between primary health centres and referral hospitals, where caesareans are performed. Similar policies have led to very high institutional caesarean rates in other sub-Saharan countries [5]. In fact, according to Burkina Faso’s Ministry of Health, the rate surpassed 40 % in some hospitals in 2013 [6]. Research has shown, however, that between 12 and 24 % of caesareans in that country are not medically indicated [7, 8].

In Burkina Faso, as in many African countries, excessive caesarean rates in some hospitals have been attributed to limited training and knowledge of personnel [7, 9]. In those facilities, it is not only obstetricians who assess indications for caesareans, but also general practitioners and nurses trained in emergency surgery (a 6-month training program involving 1 month of theoretical courses and a 5-month practicum in surgical and obstetric emergencies).

While greater access to caesareans is a necessity in countries where the national rate is below 10 % [10], it is imperative that quality improvement programs be implemented at the same time to prevent excessive and inappropriate increases in caesarean rates [11]. High rates of non-medically indicated caesareans (NMIC) are associated not only with adverse health outcomes for mothers and infants, but also with high public spending on health, presenting equity and efficiency challenges for low-resource countries [12–19].

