Various strategies for reducing the proportion of NMICs have been tested and evaluated: 1) obtaining a second opinion on the indication for a caesarean before proceeding [20]; 2) encouraging normal, midwife-assisted deliveries outside the hospital [21, 22]; 3) establishing guidelines based on recommendations of professional associations [23, 24]; and 4) auditing indications for caesareans and providing feedback to health professionals, combined with instituting best practices for managing labour and performing caesareans [25]. A meta-analysis of 10 randomized controlled trials in high-income countries showed a 19 % reduction in caesarean rates using one or a combination of the different approaches cited above. The most effective strategies were clinical audits with feedback (RR = 0.87; 95 % CI = 0.81, 0.93), continuous quality improvement strategies (RR = 0.74; 95 % CI = 0.70, 0.77), and multi-faceted interventions combining several approaches (RR = 0.73; 95 % CI = 0.68, 0.79) [26, 27].

Furthermore, the use of SMS (Short Message Service) technology appears to have a positive, and less costly, impact on the continuing education of healthcare providers in sub-Saharan Africa [28–30]. Indeed, studies on its use have shown SMS is easy to implement and produces positive results in terms of improved knowledge and practices among health professionals in different contexts [31–33].

While the results of randomized controlled trials in high-income countries are encouraging [25], we found no evidence that these interventions, whether alone or in combination, are effective in reducing NMIC rates in low- or middle-income countries.

The objective of the DECIDE (Appropriate decision for caesarean section in Burkina Faso) trial is to evaluate the effectiveness and understand the implementation of an intervention combining three potentially effective approaches for reducing NMIC rates: 1) training in best practices during labour and delivery to favor vaginal delivery for low-risk women; 2) clinical audits based on objective criteria for the main indications for caesareans; and 3) SMS-based reminders to support decisions regarding clinically indicated caesareans.

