### Assessment criteria

These criteria were measured for a 6-month period (May 2–November 2, 2014) preceding the intervention year and will be measured again in the 6 months following the end of the intervention, corresponding to the same months of the year.

The primary assessment criterion is the NMIC rate.

We conducted a literature review to discern the diagnostic reasoning underlying evidence-based indications for caesareans. The four main indications for caesareans in Burkina Faso are: previous caesarean, prolonged/obstructed labour, pre-eclampsia, and acute foetal distress. In the 22 participating hospitals in the pre-intervention study, these four indications accounted for 76 % of all caesareans performed. The relevant references [47–70] were consulted and used to generate a provisional list of good practice criteria. Preference was given to evidence obtained through randomized controlled trials, considered the most rigorous. The provisional list of criteria was sent to 16 international and national experts (gynecologist-obstetricians, midwives, and a public health physician, see Additional file 10). The experts gave their opinions on the relevance of each criterion and proposed others. The criteria retained were those validated by at least two-thirds of the experts. We then developed clinical decision trees (algorithms) for managing the four main indications for caesareans and derived the criteria for NMIC.

The NMIC criteria are presented in Table 1. For each indication, all the criteria are considered simultaneously. A caesarean is judged to be non-medically indicated when all the criteria are met or when they are not documented and no opposing medical indication is provided. The NMIC rate was calculated for each hospital. This rate is the proportion of NMICs among all the caesareans performed for the four indications during the same period.

**Table 1 Tab1:** Criteria for non-medically indicated caesareans ^a^

Previous caesarean section	Prolonged/obstructed labour

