Pre-labour caesarean not indicated if ^a^: - One previous caesarean section with transversal scar - Singleton foetus in cephalic presentation - Lack of ultrasound or clinical evidence of macrosomia - Lack of radiographic or clinical evidence of restricted pelvis - Possibility of performing emergency intra-partum caesarean section 24 h on call Caesarean during labour not indicated if ^a^: - Same criteria as pre-labour caesarean (see above) - Cervical dilation progressing normally (>2 cm in 4 h) - Presentation progressing normally at full dilation (no arrest >3 h) - Lack of evidence of foetal distress^b^ - No documented signs of uterine rupture OR Duration between full dilation and decision for caesarean delivery >3 h and no attempt of instrumental delivery (forceps or vacuum) if this is indicated	Pre-labour caesarean for presumed obstructed labour not indicated if ^a^: - Singleton foetus in cephalic presentation - Lack of ultrasound or clinical evidence for macrosomia - Lack of radiographic or clinical evidence of restricted pelvis - No documented history of fistula or uterine malformation - No documented history of uterine rupture Caesarean for failed induction or slow dilation without foetal distress is not indicated if ^a^: - Membranes intact OR - Membranes ruptured, uterine contractions adequate and time elapsed since stagnation of dilation under 4 h OR - Membranes ruptured, uterine contractions inadequate, no attempt at augmentation with oxytocin OR - Membranes ruptured, uterine contractions inadequate, augmentation with oxytocin and time elapsed since stagnation of dilation under 6 h Caesarean at full cervical dilation without foetal distress not indicated if ^a^: - Non-engagement of presentation and time elapsed between full dilation and decision for caesarean under 3 h - Engaged head and instrumental delivery (forceps or vacuum) not attemped
Pre-eclampsia	Foetal distress

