Pre-labour caesarean not indicated if ^a^: - Lack of evidence of foetal distress^b^ - Lack of clinical or ultrasound evidence of foetal growth restriction - No documented signs of severity for the woman^c^ - No documented signs of abruptio placentae Caesarean during labour not indicated if ^a^: - Same criteria as pre-labour caesarean (see above) - Cervical dilation progressing normally (>2 cm in 4 h) - Presentation progressing normally at full dilation (no arrest >3 h)	Caesarean during labour not indicated if ^a^:signs of abruptio placentae - Clear amniotic fluid or not documented -No maternal fever or not documented - Cervix dilation or presentation progressing normally - Foetal heart rate normal (120–160 beats/min.) OR abnormal but uncorrected (oxygen administration and mother on left side)

^a^All criteria are required

^b^Signs of foetal distress: foetal heart rate abnormalities (<120 or >160 beats/min. or repeated decelerations); coloured amniotic fluid

^c^Signs of severe pre-eclampsia: blood pressure ≥160/110 mmHg; albuminuria ≥3+ or ≥3 g/24 h; oliguria <30 mL/h; headache; epigastric pain; vision disorders; neurologic disorders; seizures; hemolysis; low platelet count; high liver enzymes

Secondary assessment criteria are:
*Ratio of pre-/post-labour caesareans*
Caesareans fall into three groups: 1) those planned and performed before labour; 2) urgent caesareans performed before labour; and 3) urgent caesareans performed during labour. It is expected that improvements in intrapartum care quality would be accompanied by a decrease in urgent caesareans during labour and an increase in pre-labour caesareans—hence, a reduction in the ratio of pre-/post-labour caesareans [71].

*Health professionals’ knowledge score*
We developed short case histories (vignettes) to measure health professionals’ knowledge in terms of their ability to correctly apply the main indications for caesareans: previous caesarean, pre-eclampsia, prolonged/obstructed labour, foetal distress. These knowledge/skills criteria were based on the diagnostic reasoning criteria for indications as selected by the experts. Each professional’s knowledge score corresponds to the number of correct responses for the 33 vignettes.

*Caesarean quality score*

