### Sample size calculation

This is a superiority trial, in which the intervention will be considered effective if it leads to a reduction of at least 50 % in the NMIC rate. The sample size was calculated to maximize statistical power [78]. With an α risk of 5 % (two-sided testing) and 1-β power of 90 %, and a variance inflation factor (VIF) = 3 (calculated using an average of 100 caesareans per hospital and an intra-cluster correlation coefficient (ρ) estimated at 0.02), 2,200 caesarean records and 22 hospitals are needed.

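### The pre-/post-labour caesarean ratio reads more pre-labour caesareans as better care, but success on the primary outcome can move that ratio either way

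*Protocol article*

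**What the plan says.** The primary outcome is stated under Assessment criteria: "The primary assessment criterion is the NMIC rate". Its definition there is: "This rate is the proportion of NMICs among all the caesareans performed for the four indications during the same period". The Sample size calculation section counts the intervention as effective if "it leads to a reduction of at least 50 % in the NMIC rate".

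The first secondary criterion in the same section is the ratio of pre- to post-labour caesareans. The article defines three groups: planned before labour, urgent before labour, and urgent during labour. It expects improved intrapartum care to be accompanied by "a decrease in urgent caesareans during labour and an increase in pre-labour caesareans". The same sentence then concludes that the ratio should fall.

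Table 1 gives the NMIC rules by labour status. Pre-labour rules exist for previous caesarean, for obstructed labour ("Pre-labour caesarean for presumed obstructed labour not indicated if") and for pre-eclampsia. Foetal distress has only an in-labour rule. In-labour rules exist for all four indications. The Background describes one intervention component as "training in best practices during labour and delivery to favor vaginal delivery for low-risk women".

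**The concern.** The primary outcome rewards avoiding some pre-labour caesareans and some in-labour caesareans. The secondary ratio is read on the premise that pre-labour caesareans should rise and urgent in-labour ones should fall, whether or not the operations are indicated. One number then carries two processes:

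- **Better planning.** Indicated cases move from urgent in-labour to planned pre-labour surgery. This raises the ratio.
- **Fewer NMICs.** This lowers the ratio or raises it, depending on when in relation to labour the avoided NMICs would have been done.

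Pooling planned and urgent pre-labour cases adds to the difficulty, because only the planned group matches the planning mechanism. At stake is the reading of a named secondary outcome. An intervention that works as intended could show a ratio moving against the stated expectation. A rise could also come from extra planned operations that Table 1 would class as NMIC.

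**Working it through.** **Inputs.** The article gives neither the pre-labour/in-labour split nor the timing of NMICs, so both are assumed. The Background reports that "between 12 and 24 % of caesareans in that country are not medically indicated"; 18% is the midpoint of that range. The target is a halved NMIC rate. The denominator of the ratio is taken as caesareans during labour, the only other group defined. There is no figure in the plan to reproduce for this outcome.

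**Direction, with no assumed numbers.** Let P and L be the pre-labour and in-labour counts, so R = P/L. Let a and b be the NMICs among them, and remove a fraction f of all NMICs, leaving other caesareans unchanged:

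R' = (P − f·a) / (L − f·b)

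R' < R exactly when a/b > P/L, that is, when a/(a+b) > P/(P+L). The ratio falls if NMICs are more often pre-labour than caesareans overall, rises if they are less often so, and stays put if the shares are equal. Case mix sets the sign. Because R is a ratio, collecting a fixed number of records per hospital does not alter this.

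**Illustration.** Take 100 caesareans for the four indications, P = 40, L = 60, R = 40/60 = 0.667, with 18 NMICs and 82 others. To halve the rate, x NMICs remain:

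- x/(82 + x) = 0.09, so x = 0.09 × 82/0.91 = 8.11
- removed: 18 − 8.11 = 9.89, so f = 9.89/18 = 0.549

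(Removing only 9 would halve the count but leave the rate at 9/91 = 9.9%.)

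| Pre-labour NMICs of 18 | Pre-labour after | In-labour after | Ratio | Change |
|---|---|---|---|---|
| 14 | 40 − 7.69 = 32.31 | 60 − 2.20 = 57.80 | 0.559 | −16% |
| 10 | 40 − 5.49 = 34.51 | 60 − 4.40 = 55.60 | 0.621 | −7% |
| 4 | 40 − 2.20 = 37.80 | 60 − 7.69 = 52.31 | 0.723 | +8% |

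Break-even is 40% of 18 = 7.2 pre-labour NMICs.

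**Another assumed split.** With P = 30 and L = 70, R = 0.429. Halving from 24% to 12% gives 0.234 if all NMICs are pre-labour, 0.367 if half are, 0.429 if 30% are, and 0.532 if none are. Halving from 12% to 6% gives 0.337, 0.401, 0.429 and 0.472.

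**The two mechanisms can cancel.** In the first row of the table, 32.31 + 57.80 = 90.11 caesareans remain. A pre-labour share of 40% needs 0.40 × 90.11 = 36.04. Moving 36.04 − 32.31 = 3.73 indicated cases from in-labour to planned pre-labour restores R = 36.04/54.07 = 0.667. A halved NMIC rate and better planning would then show as no change.

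**Both readings of the sentence.** If a rise in the ratio is expected, avoided pre-labour NMICs work against it (first two rows). If the literal fall is expected, avoided in-labour NMICs work against it (last row). Settling the direction does not remove the problem.

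**The case against.** **There is no success or failure rule.** A reader might infer that a successful trial would be declared a failure on this outcome. The article does not say so. It states an expectation, judges effectiveness on the NMIC rate, and includes the ratio neither in its secondary hypotheses nor in the outcomes the Analysis strategy lists for the GEE approach. This stands and limits the weight of the point. The expectation is still the only guidance given for reading the outcome.

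**The direction is unsettled.** The sentence expects component changes that raise the ratio, then a fall in it. If the fall is kept, a lower ratio after avoiding pre-labour NMICs is the expected result. True, but the conflict then comes from in-labour NMICs, so it changes source and does not disappear.

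**Table 1 cuts both ways.** A reader might infer that the intervention mainly targets pre-labour operations. The documents do not support that: in-labour rules cover all four indications, and the training component concerns care during labour and delivery. If most NMICs are in-labour, removing them raises the ratio, in line with the expected component changes.

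**The ratio can be read beside the primary outcome, and detailed tabulation may sit in a fuller document.** So it would be too strong to call the outcome uninterpretable; added unnecessary planned caesareans would also show in the NMIC rate. But the article itself fixes the pooled ratio and its interpretation, which is a stated choice and not an omission.

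**Splitting by NMIC status has a cost.** That status arises after randomisation, is what the intervention targets, and depends on documentation, since undocumented criteria can count towards NMIC. It also leaves out the 24% of caesareans outside the four indications (100% − 76%). This stands, so such a split can only be descriptive.

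**Conclusion.** The point holds as a weakness in how one secondary outcome is defined and read. With other caesareans unchanged, full success on the primary outcome can move the pooled ratio in either direction, and the timing of NMICs decides which. This is true whichever direction the sentence is finally made to state.

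The conflict is possible, not certain. It depends on a timing split that the article does not give, and a shift of indicated cases to planned surgery would not conflict with the primary outcome. In the main illustration the change runs from −16% to +8%; these sizes rest on the assumed 40/60 split, 18% NMIC rate and NMIC timings. If the ratio covers all caesareans and not only the four indications, operations for other indications would dilute the movement, and the comparison in the sign rule would be with the pre-labour share of all caesareans. The primary analysis is untouched. This is a cheap improvement worth making.

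**What to change.** 1. Reconcile the direction within the sentence: the expected component changes and the expected fall in the ratio cannot both stand.
2. Report, by arm and period, the shares of the three groups already defined (planned pre-labour, urgent pre-labour, urgent in labour), instead of the pooled ratio alone.
3. Delete the reading that an overall rise in pre-labour caesareans means improvement. Possible wording: *The distribution over the three timing groups will be reported by arm and period and read together with the NMIC rate; a higher pre-labour share is not by itself taken as better care.*
4. Add the same table by NMIC status among the four indications as a descriptive aid only, with a note that this status is itself affected by the intervention and by documentation, and that Table 1 has no pre-labour rule for foetal distress.

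This should need no new data: the three groups already require timing and urgency, and the NMIC rules already require indication and labour status. The cost is rewording one secondary outcome and reporting several shares instead of one number. No clinical criterion and no part of the primary analysis changes.

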In addition to the diagnostic reasoning criteria for caesarean indications, the expert committee also developed good-practice criteria to assess whether the caesarean was performed at the proper time and appropriately. Those criteria are presented in Table 2.

**Table 2 Tab2:** Caesarean quality criteria

ᅟ	ᅟ
− Patient must be given clear information on the indication for the caesarean. − Elapsed time between decision and incision must be no longer than 30 min. − Preference is given to using local or regional anaesthesia. − Patient receives prophylactic antibiotics. − Misgav Ladach surgical technique is used. − Joel-Cohen skin incision is used. − Delivery is done using controlled cord traction rather than manually. − In post-operative care, patients without complications resume liquid diet after 6 h. − In post-operative care, high-risk patients (morbid obesity, pre-eclampsia, history of thromboembolism) undergo thromboembolism prevention therapy.	In each hospital, all caesareans performed over the same given period will be evaluated. One point will be attributed for each criterion met (0 for those not met). For each case, total points attributed will be divided by the total number of criteria, giving a score of between 0 and 100 %. Each hospital’s quality score will be the average of the scores for all the caesareans evaluated for that hospital.

*Resource availability score*
Resource availability indicators will be measured in each hospital before and after the intervention through a systematic and standardized inventory of available resources. For each facility, a hospital environment complexity index will be calculated to reflect the availability of the different categories of resources needed to provide good-quality obstetric care [72, 73]: basic services; screening tests; basic emergency obstetric resources; intrapartum care; general medicine services; anaesthesiology; human resources; teaching and clinical resources; and clinical care protocols.

*Perinatal mortality in infants delivered by caesarean*

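### Two secondary outcomes are wrongly specified: the expected fall in the pre-/post-labour ratio contradicts its own premise, and the quality score divides by all nine criteria although two apply only to subgroups

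*Protocol article*

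**What the plan says.** Both outcomes are defined under Assessment criteria in the protocol article.

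**Ratio.** The outcome is named "Ratio of pre-/post-labour caesareans". Caesareans are divided into three groups: "1) those planned and performed before labour; 2) urgent caesareans performed before labour; and 3) urgent caesareans performed during labour". Better intrapartum care is expected to bring "a decrease in urgent caesareans during labour and an increase in pre-labour caesareans", from which the article infers "a reduction in the ratio of pre-/post-labour caesareans".

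**Quality score.** Table 2 lists nine criteria, and every caesarean in the period is scored. The rule reads "One point will be attributed for each criterion met (0 for those not met"), and for each case "total points attributed will be divided by the total number of criteria". The result is presented as running from 0 to 100%, and a hospital's score is the mean over its cases. Two of the nine criteria carry a condition in their own wording. One requires that "patients without complications resume liquid diet after 6 h". The other requires that high-risk women (morbid obesity, pre-eclampsia or a history of thromboembolism) "undergo thromboembolism prevention therapy". The article gives no category for a criterion that does not apply and no reduced denominator.

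**The concern.** The ratio's name, its expected component changes and its expected direction cannot all be right. The term post-labour also matches none of the three groups, so the reader has to infer that it means the during-labour group. If the direction is carried into the report as written, the shift the authors hope for would move against the stated expectation, and the opposite shift would agree with it.

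The quality score has a different fault. A woman to whom a criterion cannot apply has neither met nor failed it, yet the rule allows only those two values over a fixed denominator. The score then partly reflects who was operated on rather than how well. This matters because better caesarean quality is one of the secondary hypotheses, and Analysis strategy tests this score for an intervention effect. Case mix could also move: the intervention aims to change which women have a caesarean, and pre-eclampsia is both a targeted indication and one of the Table 2 risk markers.

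**Working it through.** **1. Direction of the ratio**

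Inputs, all from the outcome's own paragraph: the numerator P is pre-labour caesareans (groups 1 and 2), the denominator L is during-labour caesareans (group 3), P rises and L falls.

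Let P rise by a > 0 and L fall by b, with 0 < b < L. Then (P + a)/(L − b) > P/L exactly when aL + bP > 0, which always holds. The ratio must rise.

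Illustration per 100 caesareans (assumed figures; the article gives none):
- Before: 30/70 = 0.43. After: 40/60 = 0.67. Relative change: 0.667/0.429 = 1.56, a 56% rise.
- Inverse ratio (during-labour / pre-labour): 70/30 = 2.33 becomes 60/40 = 1.50, a fall.

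A grid of starting splits with rises and falls of up to 20 per 100 gave 6,920 combinations, and the pre-/post-labour ratio rose in every one. The stated reduction is therefore reproduced only if the ratio is inverted.

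**2. Highest attainable quality score under perfect care**

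Inputs: nine criteria (Table 2); 1 point if met, otherwise 0; denominator 9. The thromboembolism item applies only to high-risk women, the liquid-diet item only to women without complications.

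Ceiling = (9 − number of inapplicable items)/9 when an inapplicable item earns 0:

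| Woman | Inapplicable items | Ceiling as written | Applicable-criteria denominator |
|---|---|---|---|
| High-risk, uncomplicated | 0 | 9/9 = 100% | 100% |
| Low-risk, uncomplicated | 1 | 8/9 = 88.9% | 100% |
| High-risk, with complications | 1 | 8/9 = 88.9% | 100% |
| Low-risk, with complications | 2 | 7/9 = 77.8% | 100% |

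**3. Dependence on case mix**

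The shares below are assumptions; the article gives none. Let h be the high-risk share and c the share with complications. A hospital's ceiling is 1 − ((1 − h) + c)/9:
- h = 5%, c = 20%: 1 − 1.15/9 = 87.2%
- h = 30%, c = 5%: 1 − 0.75/9 = 91.7%

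Now hold care constant, with 80% of applicable criteria met and no complications:
- Inapplicable item scored 0: (8 × 0.8 + 0.8h)/9 = 71.6% at h = 5% and 73.8% at h = 30%.
- Inapplicable item counted as met: (8 × 0.8 + 0.8h + (1 − h))/9 = 82.1% at h = 5% and 81.6% at h = 30%.
- Applicable criteria only: 80% at any h.

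Both readings of the written rule miss the true 80% and move with h although care is the same. They move in opposite directions.

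**The case against.** On the ratio, the stated direction is an expectation and not a decision rule. It does not enter the calculation, no success criterion rests on it, and the test that Analysis strategy specifies is two-sided. The same sentence also gives the hoped-for component changes, so a careful reader could recover the intent. All of this stands. A reader might infer that a good result would be reported as a failure; the article does not support that, only that it could be misread. The contradiction itself remains.

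On the score, the article never says in words that an inapplicable item earns 0, and a scorer might count it as met or leave it out. Applicability coding could also be a detail left to the full protocol or analysis plan. The first point is fair, and it is why both readings were worked through. The second would carry more weight had the article been silent, but it fixes a denominator, and leaving items out does not fit the denominator as worded.

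A reader might also infer that planned caesareans automatically fail the 30-minute decision-to-incision item, so that each 10-point rise in their share costs an arm 0.10 × 1/9 = 1.1 points. Table 2 puts no such limit on that item. The figure would be an upper bound that assumes every displaced urgent case met the item. The article moreover predicts more pre-labour caesareans, which include urgent ones, and not more planned ones.

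**Conclusion.** Both points hold. The ratio's direction is wrong for the ratio as named. This follows from the sentence alone and needs no assumption. The article does not show whether the label or the direction is the slip. The consequence is a risk of misinterpretation; the estimate and a two-sided test are unchanged.

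The quality score's rule is faulty as stated. Its literal ceilings are 89% for low-risk uncomplicated women and 78% for low-risk women with complications, and the distortion is at most 1/9 (11.1 percentage points) per inapplicable item per woman. A reader might go on to conclude that the difference between arms is biased. The article does not establish that: hospitals are randomised within strata, adjustment for baseline characteristics is planned, and similar case mix in both arms would give similar distortion. The comparison could be distorted if case mix differs or shifts between arms, but neither size nor direction can be derived from the document.

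Both outcomes are secondary. The primary outcome and the sample size are unaffected.

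**What to change.** **Ratio.** Define it as pre-labour caesareans (groups 1 and 2) over during-labour caesareans (group 3) and state that an increase is expected. Alternatively, invert it and keep the expected reduction. Replace the term post-labour with the defined group.

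**Quality score.** Score each case as criteria met divided by criteria applicable to that case, then average by hospital. Fix in advance, for the liquid-diet and thromboembolism items, which cases each applies to. State whether the 30-minute item is meant to cover planned caesareans.

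**Cost.** Wording of two outcome definitions. Data collection and processing already lists maternal characteristics, diagnosed complications, the procedure and post-operative monitoring, so no new kind of data should be needed. The form itself is not shown, so confirm that it records the three risk markers named in Table 2.
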